## Abstract

**Background:**

Muscle loss and fat gain contribute to the disability, pain, and morbidity associated with knee osteoarthritis (OA), and thigh muscle weakness is an independent and modifiable risk factor for it. However, while all published treatment guidelines recommend muscle strengthening exercise to combat loss of muscle mass and strength in knee OA patients, previous strength training studies either used intensities or loads *below* recommended levels for healthy adults or were generally *short*, lasting only 6 to 24 weeks. The efficacy of high-intensity strength training in improving OA symptoms, slowing progression, and affecting the underlying mechanisms has not been examined due to the unsubstantiated belief that it might exacerbate symptoms. We hypothesize that in addition to short-term clinical benefits, combining greater duration with high-intensity strength training will alter thigh composition sufficiently to attain long-term reductions in knee-joint forces, lower pain levels, decrease inflammatory cytokines, and slow OA progression.

**Methods/Design:**

This is an assessor-blind, randomized controlled trial. The study population consists of 372 older (age ≥ 55 yrs) ambulatory, community-dwelling persons with: (1) mild-to-moderate medial tibiofemoral OA (Kellgren-Lawrence (KL) = 2 or 3); (2) knee neutral or varus aligned knee ( -2° valgus ≤ angle ≤ 10° varus); (3) 20 kg^.^m^-2^ ≥ BMI ≤ 45 kg^.^m^-2^; and (3) no participation in a formal strength-training program for more than 30 minutes per week within the past 6 months. Participants are randomized to one of 3 groups: high-intensity strength training (75-90% 1Repetition Maximum (1RM)); low-intensity strength training (30-40%1RM); or healthy living education. The primary clinical aim is to compare the interventions’ effects on knee pain, and the primary mechanistic aim is to compare their effects on knee-joint compressive forces during walking, a mechanism that affects the OA disease pathway. Secondary aims will compare the interventions’ effects on additional clinical measures of disease severity (e.g., function, mobility); disease progression measured by x-ray; thigh muscle and fat volume, measured by computed tomography (CT); components of thigh muscle function, including hip abductor strength and quadriceps strength, and power; additional measures of knee-joint loading; inflammatory and OA biomarkers; and health-related quality of life.

**Discussion:**

Test-retest reliability for the thigh CT scan was: total thigh volume, intra-class correlation coefficients (ICC) = 0.99; total fat volume, ICC = 0.99, and total muscle volume, ICC = 0.99. ICC for both isokinetic concentric knee flexion and extension strength was 0.93, and for hip-abductor concentric strength was 0.99. The reliability of our 1RM testing was: leg press, ICC = 0.95; leg curl, ICC = 0.99; and leg extension, ICC = 0.98. Results of this trial will provide critically needed guidance for clinicians in a variety of health professions who prescribe and oversee treatment and prevention of OA-related complications. Given the prevalence and impact of OA and the widespread availability of this intervention, assessing the efficacy of optimal strength training has the potential for immediate and vital clinical impact.

**Trial registration:**

ClinicalTrials.gov, NCT01489462

## Background

By 2030, an estimated 67 million American adults will report physician-diagnosed arthritis—a 40% increase in 25 years [1]. Osteoarthritis (OA) is the most common form of arthritis and the leading cause of disability among adults; the prevalence of self-reported doctor diagnosed OA in the United States is estimated at greater than 27 million persons [2]. Knee OA accounts for a significant portion of this disability, and is largely due to factors that alter knee-joint loading. Results from this project will inform future management of patients suffering from knee OA and could have enormous public health implications.

Muscle loss and fat gain contribute to the disability, pain, and morbidity associated with knee OA [3], and thigh muscle weakness is an independent, modifiable risk factor [4,5]. While treatment guidelines recommend strengthening exercise to combat sarcopenia in knee OA patients [6,7], the appropriate intensities or loads (defined as percent of one repetition maximum, or %1RM) recommended are unclear. The intensities used in previous OA studies were *below* those recommended by the American College of Sports Medicine for healthy adults [8] (60-80% 1RM). Further, the programs were generally *short*, between 6 and 24 weeks [9-16]; effect sizes were low-to-modest, changes in progression could not be detected, and they provided little lasting clinical benefit. Indeed, short-term exercise benefits are gone 6 months post-exercise [17-19] but long-term supervised exercise results in sustained benefits 2 years after the treatment ends [20]. Few have studied the effectiveness of more intense strength training due to the unsubstantiated belief that it might exacerbate OA symptoms [21]. Preliminary studies indicate that high-intensity strength training is safe and well tolerated by healthy older adults [22,23] and knee OA patients [16,24].

Greater thigh fat is associated with obesity, a major risk factor for knee OA [25]. Obesity combined with sarcopenia, termed sarcopenic obesity, is also closely associated with the prevalence of knee OA with an Odds Ratio = 3.51 [26]. Intensive strength training can change thigh composition in older adults and has shown promise in treating the underlying biomechanical (knee-joint loading) and inflammatory disease pathways. Studies in healthy older adults associate intensive strength training with increased fat-free thigh mass and quadriceps cross-sectional area and decreased percent body fat and thigh subcutaneous fat with minimal alteration in total body weight [27-30]. Sipila and Suominen [27] and Ferri et al. [23] noted increased quadriceps cross-sectional area and lean cross-sectional area, and less intramuscular thigh fat after 16–18 weeks of intensive strength training. Similarly, Treuth et al. [31-33] found increased thigh muscle mass and decreased thigh fat mass after 16 weeks of high-intensity strength training in older men and women. High-intensity strength training also reduced interleukin (IL)-18, a pro-inflammatory cytokine, in HIV-infected patients [34] and IL-6 and C-reactive protein (CRP) levels in older adults with chronic kidney disease compared to controls [35]. We must now gather clinical and mechanistic evidence to determine if improved thigh muscle composition has *long-term protective effects* on joint mechanics, inflammation, and structural progression in knee OA.

This paper describes the design of the Strength Training for ARthritis Trial (START), the first long-term clinical trial comparing the efficacy of *high-* (75-90% 1RM) to *low-intensity* (30-40% 1RM) strength training and Healthy Living Education interventions in older adults with knee OA. This trial is designed to identify potential mechanisms, (i.e. knee joint loading and systemic inflammation) responsible for any changes in pain, function, and mobility consequent to intensive strength training. We expect initial improvements in thigh muscle function, pain, and knee-joint loading with high-intensity strength training after 6 months; 18 months will determine, *for the first time*, if further changes in thigh muscle function and composition significantly reduce knee-joint forces and inflammatory cytokines resulting in a greater decrease in pain and attenuated OA disease progression (Figure 1). Given the prevalence of OA, the detrimental effects of sarcopenia and obesity [26], and the safety and widespread availability of the intervention, this trial has immediate, potentially transformative clinical impact.

**Figure 1 F1:**
[figure not shown]
Hypothesized pathways mediating high-intensity strength-training outcomes at 6 and 18 mos.

## Methods/Design

### Study design

START is an assessor-blinded, single-center, 18-month, parallel design randomized controlled trial. Participants are randomized into one of 3 groups: high-intensity strength training (H), low-intensity strength training (L), or healthy living education (C).

### Study sample

The study sample consists of 372 ambulatory, community-dwelling adults age ≥55 yrs with self-reported disability due to knee OA. Inclusion criteria include: (1) mild-to-moderate radiographic medial tibiofemoral OA (Kellgren-Lawrence (KL) = 2 or 3); (2) knee neutral or varus aligned knee ( -2° valgus ≤ angle ≤ 10° varus); (3) BMI ≥ 20 kg^.^m^-2^ and ≤ 45 kg^.^m^-2^; and (4) no participation in formal strength training for more than 30 min^.^wk^-1^ in the past 6 months. We exclude people with BMI >45 kg^.^m^-2^ because of difficulty in using CT equipment and lower adherence to exercise [36,37] and <20 kg^.^m^-2^ because of limited thigh fat. We include only people with neutral (−2° valgus to 2° varus) or moderate varus (≤ 10° varus) alignment and medial knee OA and *not* predominant lateral compartment or severe patellofemoral (PF) compartment disease because (1) the medial compartment is the most common disease site, and (2) medial progression is strongly associated with moderate varus alignment [38-40], independent of BMI [41]. People with extreme malalignment (>10 degrees varus) might experience greater progression in a strengthening program [21,42]. Medial bone-marrow lesions are seen mostly in patients with varus limbs, who are most likely to progress medially [43]. This approach will engage an enriched cohort of structural progressors to determine better our intervention’s ability to slow the disease [16]. All participants may maintain their medications, including NSAIDs. If pain decreases, they may reduce them with their physician’s consent. Medication use is recorded at baseline and 6-, 12-, and 18-month follow-up testing. Exclusion criteria are listed in Table 1. The study protocol was reviewed and approved by the Human Subjects Committee of Wake Forest University Health Sciences (Human Protocol: IRB00018176) and is in compliance with the terms and conditions set forth in the Helsinki Declaration (http://www.wma.net/en/30publications/10policies/b3/index.html). Informed consent will be obtained from all study participants.

**Table 1 T1:** Exclusion criteria

**Criteria**	**Exclusion**	**Method**
Significant co-morbid disease that would threaten safety or impair ability to participate in interventions or testing, previous acute knee injury, bilateral severe tibiofemoral OA, severe patellofemoral OA (JSN = 3 using OARSI atlas), no definite medial tibiofemoral OA, severe obesity, low weight.	Symptomatic or severe coronary artery disease; severe HTN; active cancer other than skin cancer; anemia; dementia; liver disease; COPD; peripheral vascular disease; inability to walk without an assistive device; blindness; type 1 diabetes; type 2 diabetes on thiazolidinedione agents; bilateral severe medial tibiofemoral OA (KL = 4), no definite medial tibiofemoral OA (KL = 0, 1), BMI < 20 or > 45 kg^.^m^-2^	Medical history; physical exam; PA and skyline knee x-ray; height and weight.
OA disease location and alignment restrictions: predominant knee OA other than medial tibiofemoral OA; valgus, or extreme varus alignment.	Lateral tibiofemoral OA > medial tibiofemoral OA, severe patellofemoral OA; valgus knee alignment > 2°, or varus alignment > 10°	Knee PA and skyline view x-rays, lower extremity long x-ray.
Excess alcohol use	≥ 21 drinks per week	Questionnaire
Inability to finish 18-month study or unlikely to be compliant	Lives > 50 miles from site or planning to leave area ≥ 3 months during the next 18 months	Questionnaire, interview
Conditions that prohibit CT	BMI > 45 kg^.^m^-2^	height and weight
Significant cognitive impairment	diagnosis of dementia or a MoCA score <20	Medical history, MoCA
Low Pain	Pain ≤ 3 on a scale from 0-20	WOMAC

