Disease progression is defined as change in x-ray medial TF JSW. A physician, masked to treatment group, measures JSW using automated computerized software. The software automatically delineates the joint space contour with the help of an edge-based algorithm. The area of measurement of minimum JSW is defined by 2 vertical lines and 2 horizontal lines obtained by a single click on the nonosteophytic outer edge of the medial femoral condyle and a single click on the inner edge of the medial tibial plateau close to the articular surface. Within these landmarks, the delineation of the bone edges of the medial femoral condyle and medial tibial plateau floor, in addition to the minimum JSW, are automatically obtained [85].

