##### Secondary aims

Standard repeated measures mixed models (including adjustment variables as noted above) are used for secondary aims at the 0.05 significance level, with pairwise treatment group comparisons performed at the 0.0167 significance level for testing 18 month effects. Short-term effects are determined by using contrast statements comparing 6-month treatment effect means from primary and secondary outcome models. Outcomes assessed at baseline and 18 months only (MoCa, DXA measures, and Knee PA x-ray) will be compared using an ANCOVA model for treatment effects adjusting for baseline BMI, gender, and baseline values of the outcome.

As inflammatory marker distributions are often skewed, data are log-transformed before analysis. The effect of the interventions at 18 months is determined with repeated measures mixed models and estimates obtained at each visit. For ease of interpretation, transformed log means and standard errors back to their original units are used.

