## Discussion

Despite strong evidence for the potent effect of mechanics on disease progression and symptoms [55,99], there are few interventions that target mechanical load. One such intervention is strength training. However, many still believe that strength training for knee OA in general, and high-intensity strength training specifically, may exacerbate knee pain and be deleterious to joint structure. It is critical to evaluate the potential benefit (or harm) of commonly used therapeutic interventions such as strength training. Due to conflicting data it is unclear if an increase in the total joint reaction force occurring with muscle strengthening contraction may actually *accelerate* the progression of structural changes within the joint, rather than prevent it [100]. A longitudinal study of 79 women with radiographic knee OA found that the mean absolute quadriceps strength of women with progressive OA (defined as worsening of the Kellgren and Lawrence grade over 2.5 years) was about 9% lower than those with radiographically stable OA [101]. In another observational study of 171 knee OA participants over 18 months, Sharma and colleagues [21] found that *greater* absolute quadriceps strength at baseline increased the risk of disease progression (defined as an increase in the grade of joint space narrowing in the medial or lateral compartment) in people with malaligned and lax knees (defined as >5° deviation from the mechanical axis) but not in those with neutral alignment. Since strength was not normalized for body mass, it is conceivable that the stronger participants were heavier, since absolute strength generally increases with body mass. More recently, Amin et al. [102] found no relationship between quadriceps strength and cartilage loss on MRI over 15 and 30 months anywhere except the lateral compartment of the patellofemoral joint, where increased quadriceps strength was protective against cartilage degeneration. Mikesky et al. [13] demonstrated a trend (p = 0.09) that strength training slowed joint space narrowing as measured on x-ray over 30 months in people with knee OA. It is important to recognize that they did not do intense training and did not elicit strength gains, just less strength loss, so different effects might be found in our study. Given the conflicting nature of the published literature and the public health impact of both a negative and a positive finding, the effects of strength training on pain, joint loading, and structure are critical to delineate.

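### The joint-space-width ANCOVA leaves out baseline knee alignment, which the plan calls a strong predictor of medial progression and measures in everyone

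*Protocol article*

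**What the plan says.** **Prognosis.** Study sample explains the focus on medial disease and neutral-to-varus knees partly by the statement that "medial progression is strongly associated with moderate varus alignment [38-40], independent of BMI [41". It presents the resulting cohort as deliberately enriched for structural progressors.

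**Measurement.** The X-ray section and Table 3 provide a full-length lower-extremity radiograph at baseline. The same section fixes the structural outcome: "Disease progression is defined as change in x-ray medial TF JSW".

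**Model.** Secondary aims assigns the knee PA x-ray, taken at baseline and 18 months only, to an ANCOVA "adjusting for baseline BMI, gender, and baseline values of the outcome". Alignment is not in that list. Randomization stratifies on BMI class and gender only. Primary aim mentions later models with further confounders and names patellofemoral severity and medications, but not alignment.

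**Threshold rationale.** Study sample supports the upper limit with "People with extreme malalignment (>10 degrees varus) might experience greater progression in a strengthening program [21,42", citing references 21 and 42. The Discussion reports that in reference 21 greater baseline quadriceps strength "increased the risk of disease progression (defined as an increase in the grade of joint space narrowing in the medial or lateral compartment", and that this held "in people with malaligned and lax knees (defined as >5° deviation from the mechanical axis) but not in those with neutral alignment".

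**The concern.** A baseline variable that strongly predicts the outcome is normally the first candidate for the adjustment set. Here the plan itself names the predictor, says that BMI does not account for it, and measures it in everyone because eligibility depends on it. It then specifies a model without it. BMI is in the model, but on the plan's own account it cannot stand in for alignment.

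Precision on joint-space width is at stake. The limitations part of the Discussion concedes that plain films may miss all but large differences in progression over 18 months, so residual variance that could be removed at no cost is worth removing. Alignment is also not a stratification factor, so a chance imbalance between arms would go unadjusted.

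A second, smaller issue is the reader's understanding of the alignment limit. The same reference supports a statement about knees beyond 10° in one section and is described with a 5° definition in another. The article does not explain the difference.

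**Working it through.** **Inputs from the article.** 124 per group and 80% power (Sample-size calculations, Primary outcomes); 80% retention, so 124 × 0.8 ≈ 99 per group; pairwise level 0.0167 for secondary outcomes (Secondary aims), taken as two-sided; stated detectable effect 0.46 (Sample-size calculations, Secondary outcomes).

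**Step 1: the plan's own figure.** Detectable effect = (z₁₋α/₂ + z₀.₈₀) × √(2/n) = (2.3932 + 0.8416) × √(2/99) = 3.2348 × 0.14213 = 0.4598. An exact t-test calculation gives 0.463. The stated 0.46 therefore reproduces, and it belongs to the secondary 0.0167 level.

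**Step 2: gain from adding alignment.** Let R² be the share of the stated model's residual variance in joint-space width that alignment explains. Residual variance falls by the factor (1 − R²). The equivalent sample size rises by 1/(1 − R²), and the detectable effect becomes 0.4598 × √(1 − R²), in units of the stated model's residual SD. The documents give no R², so the values below are assumptions.

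| Assumed R² | 1/(1 − R²) | Equivalent n per group | Detectable effect (SD) |
|---|---|---|---|
| 0% (as planned) | 1.000 | 99 | 0.460 |
| 2% | 1.020 | 101 | 0.455 |
| 5% | 1.053 | 104 | 0.448 |
| 10% | 1.111 | 110 | 0.436 |
| 15% | 1.176 | 116 | 0.424 |

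The low end is plausible: eligibility restricts the angle to between 2° valgus and 10° varus, and baseline width, already in the model, may carry some of the same information.

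**Step 3: what an arm-by-alignment estimate could show.** If a share p of participants lies beyond 5° varus, the smallest detectable difference in treatment effect between the two bands is 0.4598/√(p(1 − p)). The share is not given. Assuming p = 10%, 20%, 30% or 50%, the result is 1.53, 1.15, 1.00 or 0.92 SD. At 30% that is 1/√(0.3 × 0.7) = 2.18 times the main-effect figure. Such an estimate is descriptive only.

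**Step 4: the two threshold statements side by side.** Study sample: beyond 10° varus, possible greater progression in a strengthening program, references 21 and 42. Discussion: beyond 5°, malaligned and lax, association with baseline strength, reference 21. A knee beyond 10° is also beyond 5°, so both statements can be true. As described, reference 21 does not by itself supply the 10° figure. Reference 42 may, but the article does not describe it.

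**The case against.** The case for leaving the model alone is respectable. The ANCOVA already contains both stratification factors and the baseline outcome, which is standard practice. Joint-space width is a secondary outcome. Adding a prognostic covariate is optional, the gain may be as small as 0.460 to 0.455 SD, and the R² range is assumed. All of this stands, and it limits the size of the point. It does not remove it: the covariate list for this outcome is explicit, the plan itself calls the omitted variable a strong predictor, and the value is already collected.

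Stronger readings are tempting but not supported:

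- *That the article contradicts itself on 5° versus 10°.* Two references are cited for the 10° statement, one is not described, and the ranges are nested.
- *That participants between 5° and 10° varus are enrolled against a known harm.* The Discussion speaks of knees that are lax as well as malaligned, in an observational study of baseline strength rather than training. It questions the result because strength was not normalised for body mass, and it sets other studies against it. Study sample enrols moderate varus on purpose.
- *That the treatment comparison is biased.* Randomization protects it.
- *That harm in varus knees would be averaged away and the result declared safe.* This is speculation; adverse events are collected separately.
- *That a missing interaction analysis is a defect.* It may sit in a statistical analysis plan that is not shown. For WOMAC pain the article gives it no basis, since the cited finding concerns joint-space narrowing.

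**Conclusion.** The point holds as a missed, cost-free gain in precision. The stated joint-space-width ANCOVA omits a baseline variable that the plan calls strongly associated with medial progression, independent of BMI. The gain is equivalent to about 2-18% more participants (detectable effect 0.455 to 0.424 SD instead of 0.460) if alignment explains 2-15% of residual variance. That range is an assumption. The primary outcomes and the validity of the randomized comparison are unaffected.

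The threshold passages are an unexplained difference in rationale, not a strict contradiction. They need reconciling, and no view is taken here on which limit is right.

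**What to change.** 1. In Secondary aims, add the continuous baseline mechanical alignment angle of the analysed knee to the covariates of the joint-space-width ANCOVA. The cost is one sentence and one degree of freedom; the x-ray is already taken, and the angle is needed for eligibility.
2. Optionally, report one arm-by-alignment estimate with its interval, for joint-space width only and labelled exploratory. Its drawback is low precision: a detectable difference of about 1 SD if 30% of participants exceed 5° varus. It should not be offered as a test of safety.
3. Reconcile the rationale in Study sample with the description of reference 21 in the Discussion, stating what each of references 21 and 42 contributes to the 10° statement and noting the laxity qualifier. This changes wording only; no change to eligibility is proposed.
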